### Recruitment and eligibility criteria

We will recruit two hundred autistic adults via participating practices: approximately 100 to each trial arm. Autistic adults are eligible if they meet the following criteria: (1) a clinically confirmed autism diagnosis and (2) aged 18 or over. Autistic adults are not eligible to take part if they meet one or more of the following criteria: (1) have had an NHS learning disability annual health check in the last 12 months or are anticipated to attend one in the next 3 months; (2) are unable to consent for themselves and do not have a relative or supporter who can consent for them, in keeping with England’s Mental Capacity Act; (3) people in the final stages of a terminal illness; (4) their GP considers it inappropriate to invite them.

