### Sample size justification

The sample size of 200 was chosen based on the number of participants that could be recruited given the funding envelope and time available. This number compares favourably with previous health checks trials that found a difference between groups [12]. Assuming an attrition rate of 10%, the sample size was inflated to 220 (110 per arm).

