### Data analysis plan

#### Statistical analysis for quantitative analysis

We will carry out all statistical analyses in accordance with the intention-to-treat principle where all participants’ outcomes are analysed as randomised. We will report all participant flow in accordance with CONSORT statement for non-pharmacological interventions. A full statistical analysis plan will be written and signed-off before trial statisticians receive any unblinded data. The following represents a summary of the planned analyses.

The underlying structure of the data displays a two-level hierarchical structure, in which one level (participants) is nested within another (practices). Members of the same practice share contextual factors and GP conduct, meaning 2 people of the same practice are more likely to have similar data relative to two people from different practices. This clustering effect can be measured using the intra class correlation coefficient (ICC). To compare the groups for the primary outcome, taking into account the clustering effect, we will use a mixed-effects Poisson regression model that has fixed effects for cluster size, treatment allocation, age, and sex. If this model does not converge, we will reduce the number of fixed effects in the model and then (if it still does not converge) change the random cluster effect to a fixed effect.

We will conduct subgroup analyses for the primary outcome by including the subgroup variable and an interaction parameter between subgroup variable and intervention. The subgroups we will investigate are number of conditions at baseline (above median vs median or below) and presence vs absence of mental health condition at baseline.

For secondary outcomes, we will use appropriate mixed-effects regression models, depending on the outcome type. If the outcome is a questionnaire that is also assessed at baseline, the model will adjust for that baseline measure.

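### Splitting the number of baseline conditions at the sample median weakens the subgroup test if the effect changes steadily with the count, and leaves the cut-off to whoever is recruited

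*Protocol article*

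**What the plan says.** All of this is in the protocol article, mainly under Statistical analysis for quantitative analysis.

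- The primary outcome is analysed with a "mixed-effects Poisson regression model that has fixed effects for cluster size, treatment allocation, age, and sex", with practice as the cluster.
- Subgroup analyses of that outcome are done "by including the subgroup variable and an interaction parameter between subgroup variable and intervention".
- Two subgroup variables are named. One is "number of conditions at baseline (above median vs median or below"). The other is "presence vs absence of mental health condition at baseline", which is binary by nature and is not affected by this point.
- No numerical or clinical cut-off is given for the first variable, and no analysis that keeps it as a count is described.
- Under Sample size justification, the total of 200 was "chosen based on the number of participants that could be recruited given the funding envelope and time available". No effect size, significance level or power is given for any test, including this one.

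**The concern.** Nobody can be placed above or below a median until each person's number of conditions is known, so the trial will hold the full count. Reducing it to two groups before fitting the interaction treats someone just above the median the same as someone far above it. If the benefit of the health check rises or falls with the number of conditions, that gradient is what the test should detect, and the split blurs it.

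The cut-off is also whatever the recruited sample yields. Conditions are counted in whole numbers, many people will be tied at the median, and all ties go to the lower group. The two groups can therefore be well short of equal, and a person with a given count may fall on different sides in two samples from the same population.

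At stake is one of only two planned tests of who benefits more, in a trial whose size was not set by a power calculation.

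**Working it through.** **Inputs.** From the article: a total of 200, about 100 per arm (Recruitment and eligibility criteria); the split rule; the Poisson model. The article states no figure for this subgroup test, so there is none to reproduce. Its one computable design figure, 200 × 1.10 = 220 after allowing for attrition, has no bearing here. Assumed, because the article does not give them: the distribution of the baseline count and the shape and size of any interaction.

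**1. Information kept by the split.** If the log rate ratio is linear in the count X, with median m, the efficiency of the split relative to the count is approximately the squared correlation between X and the indicator D = 1 when X > m:

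r² = Cov(X, D)² / [Var(X) · p(1 − p)], where p = P(X > m).

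Worked case, Poisson with mean 3: m = 3 and p = 0.353. For a Poisson count, Cov(X, D) = mean × P(X = m) = 3 × 0.2240 = 0.672. So r² = 0.672² / (3 × 0.353 × 0.647) = 0.66, a loss of 34%.

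| Assumed distribution | Information kept (r²) | Loss |
|---|---|---|
| Normal (reference) | 2/π = 0.637 | 36% |
| Poisson, means 1 to 8 | 0.646-0.696 | 30-35% |
| Negative binomial, k = 1, 2 or 4, means 1 to 8 | 0.487-0.693 | 31-51% |

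Across these 30 count distributions (9 Poisson, 21 negative binomial), 24 lose more than one third. The other six all have a mean of 2 or less and lose 30.4-33.3%. Over the whole range, 200 participants act like 200 × 0.487 = 97 to 200 × 0.696 = 139 for this interaction.

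**2. Effect on standard error and power.** Take seven cases: Poisson means 2, 3 and 5 (r² 0.65-0.67), and negative binomial with mean 3 k = 2, mean 4 k = 2, mean 4 k = 1 and mean 6 k = 3 (r² 0.55-0.60).

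- The standard error rises by the factor 1/√r²: 1/√0.67 = 1.22 to 1/√0.555 = 1.34.
- For an interaction that would have 80% power on the count scale, power with the split is Φ(2.80√r² − 1.96). With r² = 0.67 this is Φ(0.33) = 63%. With r² = 0.555 it is Φ(0.13) = 55%.

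**3. Simulation in a Poisson model.** N = 200, 1:1, two-sided 5%, 1,000 runs, no clustering because the number of practices and the ICC are not given. The assumed interaction is in log rate per SD of the count.

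| Count distribution | Interaction | Rejected, count | Rejected, split |
|---|---|---|---|
| Poisson, mean 3 | 0 | 5.5% | 5.0% |
| Poisson, mean 3 | 0.3 | 86% | 69% |
| Negative binomial, k = 2, mean 3 | 0 | 5.4% | 5.9% |
| Negative binomial, k = 2, mean 3 | 0.3 | 90% | 71% |

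Type I error stays near 5% either way. The absolute powers are illustrative; the contrast is what matters.

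**4. Stability of the cut-off and size of the groups.** Over 20,000 samples of 200, rounding a half-integer median down because it gives the same split:

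- negative binomial k = 2, mean 2: the median is 1 in 53% and 2 in 47%;
- negative binomial k = 2, mean 3: 2 in 78% and 3 in 22%;
- Poisson mean 3: 3 in 98%.

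Instability is therefore possible but not certain. Because of ties, the upper group holds 25-50% of people across the 30 distributions.

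**5. If the interaction is not linear.** The same squared correlation, for the seven cases in step 2:

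| True shape | Linear count keeps | log(1 + count) keeps | Split keeps |
|---|---|---|---|
| Linear | 100% | 80-92% | 55-67% |
| Rises to one above the median, then flat | 54-84% | 88-94% | 59-75% |
| Step at the median | 55-67% | 53-68% | 100% |

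In the four negative binomial cases with a plateau, the split (66-75%) does better than the linear count (54-61%) but worse than log(1 + count) (88-89%).

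**The case against.** The best defence is that the loss depends on a shape the article does not state. The efficiency figure is symmetric: if the true effect is a step at the median, the split is the right model and a linear count keeps only 55-67%. The outcome is needs newly detected and met, so a steady gradient cannot be taken for granted. This stands, and it is why the loss has to be stated conditionally. It does not make the split the better default, because a step exactly at the sample median is a special case, and log(1 + count) does better than the split under the linear and plateau shapes in all seven cases.

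Second, the rule is fixed in advance on a baseline variable and says where ties go, which prevents searching for a cut-off. This also stands. A reader might infer that a data-derived cut-off inflates false positives; the simulation does not show this. A reader might also infer that the result could not be carried to another population. That is too strong: once the realised median is reported, others can apply the same number. What remains is limited comparability.

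Third, choosing between a linear and a log scale after seeing how skewed the counts are would be sample-dependent too. That is right, and the scale must be fixed beforehand.

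Fourth, the section calls itself a summary, with a full SAP to follow. The SAP may add a count-scale test, but it is not shown. The article does not leave the form of the variable open; it fixes the split.

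**Conclusion.** The point holds in conditional form. The article fixes a median split as the form in which number of conditions enters the interaction, with no external value for the median. If the log rate ratio changes roughly steadily with the count, the split loses about 30-50% of the information for that test, under assumed Poisson or negative binomial counts. A reader might want to say flatly that a third or more is discarded. The documents do not support this, because they give neither the distribution nor the shape: the loss is slightly under a third at some low mean counts and zero for a step at the median. Likewise, the fall from 80% power to 55-63% illustrates the contrast and does not estimate this trial's power.

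The realised cut-off may differ between samples, which limits comparability. Nothing in the article is miscalculated or contradictory here. The primary comparison, the sample size and the other subgroup test are untouched. Severity: minor to moderate.

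**What to change.** In the SAP, before any unblinded data reach the statisticians:

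1. Make the interaction of arm with the number of baseline conditions, entered as a count, the subgroup test.
2. Fix its scale now, linear or log(1 + count), and do not let the observed skewness decide.
3. Report the rate ratio with its interval at two or three counts named in advance.
4. Keep the median split for descriptive display only, and report the realised median and the number of people in each group.

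This takes a few lines of text and needs no new data, no extra participants and no change in conduct. The price is an assumed shape for the interaction. A plot can be used to check it, but with about 200 clustered participants the check will be rough, and a true step near the median would be detected less efficiently than with the split.

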### Randomisation

Practices will be randomised to the intervention (health check) arm or the control (usual care) arm prior to participant recruitment via computer-generated sequence blocks [2, 4, 23]. Randomisation will be stratified by practice list size (small < 10,000 and large ≥ 10,000). A member of the research team independent of trial data collection will oversee this process and inform the practices of the randomisation outcome. The research team will make autistic participants aware as to whether they are in the health check or usual care arm in the study information pack. Due to the design of this trial, it is not possible for practices or participants to remain blinded to group.

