Participants who withdraw consent for the collection of routinely available data prior to month 9 will not be included in the primary outcome analysis. We do not anticipate there being missing data for the primary outcome as it is based on routinely collected data. Secondary analyses will be complete-case analyses. For outcomes that are significant, if there is substantial differential dropout between treatment groups, we will apply multiple imputation with at least 20 imputed datasets and undertake sensitivity analyses to explore the robustness of results to the missing not at random assumption. We will record and tabulate the number of serious adverse events per group.

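### For secondary questionnaire outcomes, multiple imputation and missing-not-at-random checks run only after a significant complete-case result, so an effect masked by dropout goes unexamined

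*Protocol article*

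**What the plan says.** All of this is in the protocol article, under Statistical analysis for quantitative analysis, unless another section is named.

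- Default for secondary outcomes: "Secondary analyses will be complete-case analyses".
- When more is done: "For outcomes that are significant, if there is substantial differential dropout between treatment groups, we will apply multiple imputation". The number of imputations is set at 20 or more, and analyses for data missing not at random are tied to the same trigger. Both conditions, significance and unequal dropout, must hold.
- Primary outcome: "We do not anticipate there being missing data for the primary outcome as it is based on routinely collected data". The one stated exclusion is withdrawal of consent for routine data before month 9.
- Guiding principle: analyses are "in accordance with the intention-to-treat principle where all participants’ outcomes are analysed as randomised".
- Randomisation section: "it is not possible for practices or participants to remain blinded to group".

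Nothing else in the article plans imputation or a missing-not-at-random analysis for a non-significant outcome. The data-handling text under Outcome measures covers missing items within a returned questionnaire, not missing questionnaires. A full analysis plan is promised, but this rule is stated outright and is not a detail left to that plan.

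**The concern.** A sensitivity analysis should ask whether a conclusion survives other assumptions about the missing data. Here, whether the question is asked depends on the p-value that the missing data may have distorted. A false positive caused by dropout can be caught. A false negative cannot, because a non-significant complete-case result ends the enquiry. The stronger the bias towards zero, the less often the check runs.

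The second condition, "if there is substantial differential dropout between treatment groups", closes another route. If both arms lose a similar share of participants but for different reasons, completers are no longer comparable, yet the dropout rates give no signal.

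This matters here because participants know their arm and quality of life and general health are questionnaire outcomes. Control participants who are doing badly, or intervention participants who feel they have no further need, could stop responding for arm-specific reasons. A biased null on quality of life would then be reported without any check.

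**Working it through.** **1. What the rule does**

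| Complete-case result | Substantial differential dropout? | Imputation and MNAR analyses run? |
|---|---|---|
| Significant, either direction | Yes | Yes |
| Significant | No | No |
| Not significant | Yes | No |
| Not significant | No | No |

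A significant reversal with substantial differential dropout is examined. A masked effect or a non-significant reversal is not.

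**2. The only dropout figure in the article.** Sample size justification assumes 10% attrition: 200 × 1.10 = 220, or 110 per arm, which reproduces. It gives no rate by arm, and no effect size, SD, power or significance level. Everything below therefore rests on assumed inputs.

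**3. Closed-form illustration.** Assumed: 110 per arm, SD 1, two-sided 5% level, clustering ignored, dropout 10% in control and 25% in intervention. Intervention dropouts are better off than intervention completers by m SD.

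- Complete-case effect = d − 0.25 × m
- SE = √(1/n_C + 1/n_I), with n_C = 110 × 0.90 = 99 and n_I = 110 × 0.75 = 82.5, so SE = √(1/99 + 1/82.5) = 0.149
- P(skipped) = 1 − [Φ(effect/SE − 1.96) + Φ(−effect/SE − 1.96)]

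Worked case, d = 0.3 and m = 0.5: effect = 0.3 − 0.125 = 0.175; 0.175/0.149 = 1.17; P(significant) = 0.217; P(skipped) = 0.783.

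| True effect (SD) | Full-data power | Skipped: 10% dropout in both arms, no bias | Complete-case effect, m = 0.5 to 1.0 | Skipped, m = 0.5 to 1.0 |
|---|---|---|---|---|
| 0.3 | 60% | 44% | 0.175 to 0.05 | 78% to 94% |
| 0.4 | 84% | 20% | 0.275 to 0.15 | 55% to 83% |
| 0.5 | 96% | 6% | 0.375 to 0.25 | 29% to 61% |

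The third column matters for reading the last one: part of the skipping is ordinary lack of power. The bias and the extra dropout account for the rise from the third column to the last.

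**4. Simulation with dropout that imputation can recover.** Assumed: 100 per arm, true effect 0.3 SD, correlation 0.7 between the 3- and 9-month scores, control dropout depending on a poor 3-month score, 10% random intervention dropout, clustering ignored. Imputation uses the 3-month score.

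| Control dropout | Complete-case effect | Imputed effect | Skipped by the significance condition |
|---|---|---|---|
| 10% | 0.26 | about 0.3 | about 46% |
| 25% | 0.16 to 0.19 | about 0.3 | 71% to 76% |

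The loss of effect is 0.30 − 0.26 = 0.04 SD in the first row. In the second it is 0.30 − 0.19 = 0.11 to 0.30 − 0.16 = 0.14 SD. A separate run of the same mechanism, with baseline correlation 0.5 and about 23% control dropout, gave 0.17 complete-case against 0.30 imputed and power of 23% against 62%. The check was skipped in 77% of trials, and imputation would have been significant in 50% of those.

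**5. Near-equal dropout.** In that same run with about 8% control dropout against 10% in the intervention arm, the complete-case effect was 0.25 against 0.30 imputed, and power 50% against 66%. Rates this close would probably not count as substantially different, so the second condition would stop the check even where the result was significant.

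**The case against.** Several points on the other side stand.

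- **The primary outcome is largely outside this.** It comes from GP records, as do other record-based outcomes, which questionnaire dropout does not remove. A reader might infer that the main result is at risk; the article does not support that.
- **A masked effect is not bound to be missed.** A reader might infer that a complete-case estimate biased towards zero must be non-significant, or that a reversal is never examined. Neither follows. Attenuation lowers the chance of significance without removing it, and a significant reversal with substantial differential dropout would be checked.
- **The larger figures describe an adverse case.** The article plans for 10% attrition overall. With 10% control dropout that depends moderately on the 3-month score, the complete-case effect is still about 0.26 to 0.27 SD. Falling to 0.19 or below needs dropout well above plan or strong selection.
- **The article does not require a different main analysis.** It already plans mixed-effects models for secondary outcomes and does not exclude repeated measures. Only the EQ-5D-5L and SF-36v2 are confirmed in the text as collected at 3, 6 and 9 months; the schedule for the other questionnaires is in a figure not shown. A fixed missingness threshold, and a definition of substantial, can be left to the analysis plan.
- **Unequal dropout will be visible**, because participant flow is to be reported to CONSORT.

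None of this answers the core point. Reporting dropout does not show its effect on the estimate, and an analysis plan that follows the article's rule inherits the asymmetry.

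**Conclusion.** The concern holds for the secondary questionnaire outcomes. The article makes a robustness check depend on the result it is meant to test, so missing data are examined for positive findings and ignored for null ones. It also relies on a difference in dropout rates, which misses differences in reasons.

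On the assumed inputs, with a true effect of 0.3 SD, the bias is modest at the planned attrition level (about 0.26 SD against 0.3) and sizeable at 25% control dropout (0.16 to 0.19 SD). The check is skipped in about 46% and 71 to 76% of trials. These are illustrations, not predictions: they depend on the assumed selection, correlations and effect size. Ignoring clustering probably understates the skipping, since clustering widens standard errors.

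This should be changed, but it does not threaten the primary analysis.

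**What to change.** Delete the opening significance condition from the imputation sentence. Prespecify, for secondary questionnaire outcomes and whatever the p-value:

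- multiple imputation that includes arm, practice, baseline score and any earlier follow-up scores collected;
- missing-not-at-random sensitivity analyses;
- a trigger based on the amount of missing data, not only on a difference in dropout rates between arms, with the level set in the analysis plan before unblinded data are received.

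Where an instrument is collected at the earlier visits, a repeated-measures mixed model using all follow-up scores is an acceptable alternative to imputation; the missing-not-at-random analyses would still be needed.

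The cost is a change of wording and a little more analysis time. No new data are needed.

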#### Economic evaluation

The economic evaluation will involve a within-trial economic evaluation to estimate the incremental cost per QALY gained at 9 months. The analysis will take the perspective of the UK National Health Service (NHS) and Personal Social Services. We will consider a wider societal perspective by analysing the costs borne by the participants and their carers. For the within trial economic evaluation, QALYs will be estimated from responses to the EQ-5D-5L administered at baseline and 3, 6, and 9 months follow-up. As per the National Institute for Health and Care Excellence (NICE)’s current guidelines [35], the EQ-5D-5L results will be converted (‘cross-walked’) into EQ-5D-3L scores. These values will be used to estimate QALYs for each participant using the area under the curve approach [36]. In a sensitivity analysis, QALYs will also be estimated from responses to the SF-36v2 administered at the same time points. The responses to the SF-36v2 will be converted into SF-6D tariffs [37] and QALYs estimated using the same methodology as described above.

Intervention cost data: The cost of delivering the health check in primary care will be calculated using the information captured by the Health Check Evaluation Questionnaire. This includes data relating to the training required for delivering the health check and the time and resources for delivering the health check appointment and creating the health action plan.

Resource use data: The costs of all health services will be estimated using routine data sources, e.g. Unit Costs of Health & Social Care for primary and social care [38], NHS National Schedule of Reference Costs, and the British National Formulary for medications [39]. For each participant, we will combine measures of the use of resources with unit costs to provide a cost for that participant and mean cost at 9 months for each randomised group.

